## Abstract

**Public clinical trial registry:**

Affective Dysregulation (AD) in Children With ADHD Treated by Guanfacin, ClinicalTrials.gov ID NCT04016207.

## Introduction

### Scientific background

The terms “affective dysregulation (AD)” and “irritability” are often used interchangeably in the international literature. Most definitions of AD characterize it as a state of excessive reactivity to negative emotional stimuli, comprising both an affective component (anger) and a behavioral component (aggression). This means that individuals with AD tend to respond to provocations with exaggerated anger and aggressive behavior. AD or irritability is a criterion for many DSM-5 and ICD-10 diagnoses in children and adults, including mood and anxiety disorders, attention-deficit/hyperactivity disorder (ADHD), and oppositional-defiant disorder/conduct disorder (ODD/CD) (1).

Symptoms of AD are most prominently observed in ODD/CD (2, 3). Approximately 6% of adolescents (11–19 years) reported significant affective lability and 5.5% of parents reported that their children (8–19 years) exhibit frequent, rapid mood swings and irritability (4). The full diagnostic criteria of DSM-5 “disruptive mood dysregulation disorder” (DMDD) are met by 0.8% to 3.3% of children and adolescents. However, the prevalence of severe anger outbursts and chronic negative mood irritability is significantly higher, often alongside with comorbid psychiatric disorders (5).

Population-based studies indicate that the prevalence of disruptive behavior disorders ranges from 14% to 35% in children with ADHD, 14%–62% in children with anxiety disorders, and 9% to 45% in children with mood disorders (6). Moreover, children and adolescents with ODD/CD often exhibit symptoms of post-traumatic stress disorder at elevated rates. Children and adolescents with externalizing behavior disorders report lower levels of psychosocial well-being compared to their peers in the general population (7).

From both clinical and scientific perspectives, the AD concept fits well within the framework of the National Institute of Mental Health Research Domain Criteria (RDoC) Initiative (8). The RDoC approach focuses on dimensional constructs that span multiple diagnostic levels and can be examined in and across different areas and interfaces. Notably, the current RDoC includes the construct of frustration due to lack of reward within the broader domain of negative emotionality.

Guanfacine is an approved pharmacological treatment for ADHD in Germany. It is approved for patients aged 6–17 years as a second-line medication when methylphenidate or other stimulants are ineffective or poorly tolerated.

Guanfacine is a selective alpha-2A receptor agonist (9) with pharmacological properties similar to those of clonidine. Clonidine, a well-established antihypertensive medication, acts on alpha-2 receptors in the brain, thereby reducing peripheral vascular resistance, which results in lower blood pressure. In the United States, unlike in Germany, clonidine is also approved for the treatment of ADHD. Its therapeutic effect in ADHD is thought to arise from an increase in noradrenergic tone in the prefrontal cortex (PFC), facilitated through direct binding to postsynaptic alpha-2A adrenergic receptors and indirect increase of norepinephrine input from the locus coeruleus (10). Guanfacine exerts its effects by selectively activating alpha-2A adrenoceptors in the central nervous system, leading to reduced peripheral sympathetic nervous system activity, as evidenced by decreases in both systolic and diastolic blood pressure (11). In ADHD, guanfacine enhances attentional regulation and behavioral control via its action on the prefrontal cortex. These strengthening effects on prefrontal cortical functions are thought to result from inhibition of intracellular cAMP signaling (12, 13).

Clonidine has been shown to reduce AD-like symptoms, such as hyperarousal or aversive inner tension in adults with borderline personality disorder (14, 15). AD represents a transdiagnostic dimension characterized by excessive reactivity to negative emotional stimuli, involving both an affective (anger) and a behavioral component (aggression). This construct is not limited to behavior in borderline personality disorder, but is also observed in ADHD and social behavior disorders. As described above, guanfacine shares significant pharmacological similarities with clonidine. However, unlike clonidine, guanfacine is approved in Germany for the treatment of ADHD in children and adolescents aged 6–17 years. These pharmacological and clinical parallels led us to hypothesize that guanfacine could reduce AD symptoms in ADHD.

In ADHD, treatment with stimulants, particularly methylphenidate, is highly effective in reducing the core symptoms of attention deficit, hyperactivity and impulsivity (16). Nevertheless, approximately 30% of patients with ADHD exhibit an inadequate response to monotherapy in clinical studies (17). A common explanation for this can be the comorbidity of ADHD and ODD/CD. In case of hyperkinetic conduct disorder, which describes this common comorbidity, methylphenidate usually treats the core symptoms of ADHD, while the ODD/CD component is less significantly changed [MTA (18)]. Effective treatment of ODD/CD often requires long-term psychosocial interventions with either behavioral treatment or support in educational processes in the family and at school (19).

The core symptoms of ODD/CD exhibit substantial overlap with the concept of AD. In severe cases, off-label psychopharmacological interventions are commonly employed in Germany, particularly given the limited efficacy of purely psychosocial long-term interventions. Despite this, there is currently no approved pharmacological treatment for this indication. Antipsychotics, such as risperidone, are often prescribed for managing severe ODD/CD (20). However, their use in children and adolescents has often been criticized due to well-documented long-term metabolic side effects (21).

### Research question

In this study, we hypothesize that patients with ADHD who demonstrate an inadequate response to methylphenidate often present with comorbid ODD/CD and, as such, exhibit elevated levels of AD. Given that guanfacine is an approved treatment for ADHD and that emerging evidence suggests its potential efficacy in managing AD, we further hypothesize that guanfacine may alleviate AD symptoms in an ADHD subpopulation that is refractory to methylphenidate and other stimulants.

To date, no studies have specifically investigated the direct effects of guanfacine on AD in patients with ADHD. However, studies in patients with autism spectrum disorder have reported reductions in oppositional-defiant symptoms following guanfacine treatment (22, 23). A meta-analysis of alpha-2 receptor agonists revealed a significant effect of guanfacine monotherapy on oppositional symptoms in ADHD. No significant effect was found for clonidine (24). For guanfacine, a mean effect size of 0.51 (Hedges’ g) was reported, based on a single study (25).

### Aims of the study

In clinical practice, treating physicians prescribe guanfacine to children and adolescents with ADHD who have not responded adequately to stimulant therapy. The primary aim of this study is to investigate whether AD was changed as a side effect (in the sense of an epidemiological observation), as measured before (T1) and after (T2) dosing, while the main effect of guanfacine is on ADHD—core symptoms. Four different measurement instruments will be used to assess AD:
1.DADYS (parent and self-report versions): This instrument is part of the ADOPT consortium's efforts to systematically investigate AD in children and adolescents. The DADYS screen is intended to assess AD in children and adolescents. So far, the tool has been validated in a sample of children 8–12 years old (26).2.Conners Comprehensive Behavior Rating Scales–Third Edition (Conners-3): A widely recognized and validated instrument for assessing ADHD and its comorbidities, the Conners-3 explicitly evaluates symptoms of conduct and oppositional-defiant behaviors, which are closely related to affective dysregulation. Both parent and self-report versions are used.3.Emotion Regulation Questionnaire for Children and Adolescents (ERQ-CA): Emotional instability, a construct that is developmentally related to affective dysregulation, is measured using this internationally established instrument. Although precursor symptoms of emotionally unstable personality disorder typically manifest later in adolescence, this tool is appropriate for the study's target age group of 6–17 years.4.Child Behavior Checklist-Dysregulation Profile (CBCL-DP): Extracted from the CBCL-6–18R parent questionnaire, this measure assesses the domains of anxious/depressed mood, attention problems, and aggressive behavior. The CBCL-DP is an established and extensively validated tool for assessing dysregulation in children and adolescents, serving as a complement to the DADYS instrument, which is still undergoing evaluation in the ADOPT consortium.In summary, the combined use of these four instruments allows for a comprehensive examination of AD directly as well as of two important clinical manifestations, ADHD in conjunction with ODD/CD and with emotional instability.

## Methods and analysis

### Study design

This is a non-interventional test in accordance with German Arzneimittelgesetz (AMG) §4(23). The design is multicentric, prospective, open, single-arm, longitudinal.

### Primary objective of the study

Change in DADYS-EF (Affective Dysregulation Questionnaire) between Visit 1 and Visit 2.

### Secondary objectives of the study

Changes between visits 1 and 2 in
•DADYS-KF.•CBCL-DP.•C3-L, child version, domains inattention, hyperactivity/impulsivity.•C3-L, parent version, domains inattention, hyperactivity/impulsivity.•C3-L, child version, oppositional behavior/aggression domains.•C3-L, parent version, oppositional behavior/aggression domains.•ERQ-CA.

### Number of patients

*N* = 40.

### Study population

The study population consists of children and adolescents aged 6–17 years with ADHD and clinically significant AD, who are treated with guanfacine by their treating physician for clinical indications and as part of regular clinical treatment. The observational study influences neither the diagnosis of ADHD nor the decision to and implementation of therapy with guanfacine. These processes remain entirely within the responsibility of the treating physician. The study team only recruits patients for observational purposes once the treatment decision has already been made.

Guanfacine is in Germany approved as second-line therapy for ADHD in cases where stimulant treatments has been ineffective or stimulants should not be prescribed. Clinical experience suggests that rates of AD are high among ADHD patients who do not respond adequately to stimulants. Given the regulatory approval of guanfacine for patients with ADHD aged 6–17 years, only children and adolescents within this age range are eligible for inclusion. While gender differences may occur, they are not anticipated to have a fundamental impact on study outcomes. Therefore, to ensure an adequate sample size and generalizability of findings, both boys and girls will be recruited.

### Inclusion criteria

•Male and female patients aged 6–17 years.•Diagnoses F90.0 (ADHD) or F90.1 (hyperkinetic disorder of social behavior).•Patients have not responded adequately to stimulants or these are not suitable for clinical reasons; switching to guanfacine is clinically indicated and regularly planned.•Patients show clinical symptoms of affective dysregulation.•IQ is at least 70.•Written informed consent from the participating patients and their legal guardians.

### Exclusion criteria

•Unipolar depression, bipolar disorder, schizophrenia, or another psychotic disorder.•Current substance abuse.

### Recruitment of patients

Children and adolescents diagnosed with ADHD who are receiving routine care at the outpatient clinic, day clinic or inpatient ward of the three study centers will be recruited: Department of Child and Adolescent Psychiatry, University Hospital Dresden, Department of Child and Adolescent Psychiatry, LWL-Klinikum Marsberg and Department of Child and Adolescent Psychiatry, Klinikum Lippe, Bad Salzuflen. In addition, practicing child and adolescent psychiatrists will be invited to identify eligible patients under their care who are planned to receive guanfacine as part of standard clinical treatment and who may be interested in participating in the study.

### Treatment with guanfacin as part of the regular clinical treatment (not part of the study)

Guanfacine treatment is conducted exclusively as part of routine clinical care in accordance with its regulatory approval and the current product information. In Germany, extended-release guanfacine “Intuniv” is approved. The treating physician retains sole responsibility for all aspects of patient care, including the diagnosis of ADHD, initiation of guanfacine therapy, obtaining informed consent, monitoring treatment response and side effects, ensuring patient safety, assessing clinical outcomes, and deciding on continued treatment. These processes are independent of the study team and explicitly not part of the observational study protocol. The following description of routine guanfacine treatment is provided for context to facilitate understanding the observational study protocol.

Guanfacine is administered exclusively as part of routine clinical care in child and adolescent psychiatry, independent of the observational study. It is regularly employed as a second-line treatment for patients with severe or treatment-resistant ADHD, as per its approval conditions. This practice is established both in Germany and at the participating study centers, and is completely independent of our observational study. The patients typically have a long history of treatment, as guanfacine is only approved for use in cases where there is a confirmed diagnosis of ADHD and an insufficient response to stimulants (methylphenidate, amphetamines), making it a second-line pharmacological treatment. These patients can be treated in outpatient, day-care or inpatient settings; their treatment history (patient is admitted to hospital from outpatient treatment for single-dose guanfacine) often includes a combination of these care levels. In other cases, practicing child and adolescent psychiatrists refer patients with ADHD to inpatient care for guanfacine dosing.

The decision to initiate guanfacine is solely made by the treating physician. However, in real practice, the decision does not lead to an immediate regulation, leaving time to assess study inclusion. Specifically, the decision is reviewed by the responsible senior physician, followed by laboratory testing, an ECG and, if necessary, a physical examination. The legal guardians will be provided with comprehensive information about the planned medication. This will include a detailed discussion of the potential effects, risks, and side effects, which will be documented. The entire process from treatment decision to guanfacine initiation typically spans 2–3 weeks. If patients and their legal guardians have previously consented to being contacted regarding research studies, the treating physician informs the study team about an eligible patient. At this point, the physician also assesses and documents whether clinically relevant symptoms of AD are present.

During the remaining interval prior to treatment initiation, the study team approaches the patient and their guardians to clarify interest and obtain consent for participation in the observational study. If consent is granted, the first measurement (T1) takes place before the start of guanfacine treatment. Importantly, the decision to use guanfacine and the entire treatment is solely under the responsibility and direction of the treating physician. Neither the inclusion in the study nor the results of the psychometric measurements (T1 and T2), which are not known to the treating physician, influence the guanfacine treatment or further treatment with guanfacine.

Guanfacine is administered according to the drug approval in Germany. The dosage in children and adolescents is up to 7 mg. During titration, an increase or decrease of 1 mg guanfacine per week is allowed.

Figure 1 illustrates the parallel processes of regular clinical treatment and observational study, whereby the observational study does not influence the regular clinical treatment.

**Figure 1 F1:**
[figure not shown]
Overview of the study design.

### Study visit 1 (T1, day 1)

Prior to inclusion in the study, all patients and their guardians must receive comprehensive information about the study. This information will be provided personally by the treating doctor and in written form via patient information materials. Only after all questions from the patient and legal guardian have been fully clarified, will they be asked to sign and date two copies of the consent form (for patients and for legal guardians) by hand. One copy of the patient information/consent form will be handled to the participant, while the second copy will be retained in the study center's records.

During visit 1, demographic data and relevant clinical documentation, including the diagnosis and indication for guanfacine treatment, are recorded. Information regarding existing AD will be collected from the reports of the treating physician and used to eligibility for the study. Once the inclusion and exclusion criteria have been thoroughly evaluated, the participating person is included in the study. The intelligence quotient will be extracted from existing clinical records.

The following psychometric instruments are collected with the patient and a parent:
•DADYS-EF.•DADYS-KF.•C3-L, children's version.•C3-L, parent version.•ERQ-CA.

### Study visit 2 (T2, day 70 ± 2)

At Visit 2, the treating physician's documentation of guanfacine dosage will be recorded.

The following psychometric instruments will again be administered to the patient and a parent:
•DADYS-EF.•DADYS-KF.•C3-L, children's version.•C3-L, parent version.•ERQ-CA.

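### CBCL-DP change is a secondary objective, but the CBCL parent form is on neither visit's instrument list, so the two parts of the protocol must be reconciled

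*Protocol article*

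**What the plan says.** Under Aims of the study, the article announces the instruments with "Four different measurement instruments will be used to assess AD". The fourth is introduced as "Child Behavior Checklist-Dysregulation Profile (CBCL-DP): Extracted from the CBCL-6–18R parent questionnaire". The same item explains why it is there: it is described as "serving as a complement to the DADYS instrument, which is still undergoing evaluation in the ADOPT consortium".

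Under Secondary objectives of the study, the list opens with "Changes between visits 1 and 2 in" and begins "DADYS-KF.•CBCL-DP.•C3-L, child version, domains inattention, hyperactivity/impulsivity". The CBCL-DP is therefore an endpoint in its own right, defined as a change between two visits.

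The section on Study visit 1 introduces its instruments with "The following psychometric instruments are collected with the patient and a parent" and lists "DADYS-EF.•DADYS-KF.•C3-L, children's version.•C3-L, parent version.•ERQ-CA". The section on Study visit 2 uses the lead-in "The following psychometric instruments will again be administered to the patient and a parent" and gives the same five entries.

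**The concern.** A change score needs a measurement at each of the two visits. The CBCL-DP has its own source questionnaire, a parent form that is not among the five listed, and the article gives no way of deriving it from those five. Someone who ran the visits from the two lists would not hand out the CBCL, and this secondary objective would have nothing to analyse.

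Two things give the omission some weight. First, the CBCL-DP has a specific job: it is the well-validated companion to the DADYS, which supplies the primary endpoint and is still being evaluated. The Aims section also says the DADYS has so far been validated only in children aged 8–12, while the inclusion criteria admit ages 6–17. Second, Visit 1 takes place before guanfacine is started. A parent rating not taken then cannot be obtained later, so any real gap grows with each patient enrolled.

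**Working it through.** The protocol gives no figure to reproduce here. The check compares the forms that the objectives require with the forms that the visits collect.

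| Form | Required by | Visit 1 list | Visit 2 list |
|---|---|---|---|
| DADYS-EF (parent) | Primary objective | yes | yes |
| DADYS-KF (child) | Secondary objective | yes | yes |
| CBCL-DP (from the CBCL 6-18R parent form) | Secondary objective | **no** | **no** |
| C3-L, child | Two secondary objectives | yes | yes |
| C3-L, parent | Two secondary objectives | yes | yes |
| ERQ-CA | Secondary objective | yes | yes |

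- Forms required: 6. Forms listed at each visit: 5. The difference is 6 − 5 = 1, and at both visits it is the CBCL.
- Secondary objectives: DADYS-KF (1), CBCL-DP (1), C3-L child (2), C3-L parent (2), ERQ-CA (1), which makes 7. Those with a listed source: 7 − 1 = 6.
- T1–T2 pairs for the CBCL-DP, if the lists are complete: 0 of at most 40, the planned sample size.

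The next step is to look for another source in the text.

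- The Visit 1 section takes IQ from existing clinical records. It says this of no other test score.
- Information on AD from the treating physician's reports is used to judge eligibility. It is not described as a CBCL score, and it would not supply a Visit 2 value.
- The Visit 2 section adds only the documented guanfacine dose.
- The Benefit-risk assessment limits data collection to rating questionnaires completed by patients and caregivers, which points back to the visit lists.

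The multiple imputation mentioned under Population for analysis would not help. A scale with no observed values at either visit leaves nothing in the trial from which to impute it.

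**The case against.** The strongest reply is that this is a slip in writing and that the form is in fact collected. The text is a journal article that condenses a fuller protocol, which is not shown. Figure 1, the design overview, is not reproduced either. Sites would work from the full protocol and the eCRF. The aims and the secondary objectives both state the intention to use the CBCL-DP, so one line dropped from a list that was then repeated for the second visit is a plausible explanation.

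This stands as far as it goes. A reader might infer from the visit lists that all CBCL-DP data will be missing. The documents do not establish that; it follows only if the lists are complete. The reply does not remove the contradiction, though. The article did not leave the instrument list to another document: it states the list twice, and every other endpoint form appears both times.

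A reader might also infer that the assessment of AD as a whole is undermined. That goes too far. The primary endpoint is on both lists, the sample size does not depend on the CBCL-DP, and the secondary objectives give it no rank above the others. The Aims section also describes the Conners-3 as validated and the ERQ-CA as internationally established, and reports some validation of the DADYS itself. The C3-L oppositional and aggression domains, which it treats as closely related to AD, remain at both visits in parent and child versions. What would be lost is narrower: on the Aims section's own summary, the Conners-3 and ERQ-CA mainly cover related clinical manifestations, so the two DADYS forms would be the only direct measures of AD left.

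**Conclusion.** The point holds as an internal inconsistency. The aims and secondary objectives require a CBCL-DP score at both visits, both visit lists omit the form it comes from, and the article describes no other source. One of the two parts is wrong.

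The size depends on which. If the lists are complete, one of seven secondary objectives has no data, and baselines already missed are lost for good. If the form is collected, the error is confined to the two lists and no data are affected. The documents shown do not settle which applies. In either case the primary endpoint and the other six secondary objectives are untouched. This should be fixed, and promptly because a missed baseline is irreversible, but it does not put the trial's main result at risk.

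**What to change.** First confirm whether the CBCL 6-18R parent form is being collected at both visits.

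- If it is, add it to the instrument lists under Study visit 1 and Study visit 2, and check that it is in the eCRF.
- If it is not but is still wanted, add it to both lists and to the eCRF now. Report how many patients were already past Visit 1 without it, because they cannot contribute to this endpoint.
- If it is not collected and will not be, remove the CBCL-DP from the Aims and the Secondary objectives, and change the count of four AD instruments to three.

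If the form is already collected, the cost is a text correction. If collection has to start, it is one more parent questionnaire at each of two existing visits. The last option costs one secondary endpoint.
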